**7.2.3 Pregnancy**

Participants who become pregnant during the trial will no longer be eligible for laser treatment but can continue for follow up if they wish to do so. The patient will continue to receive standard of care.

Pregnancy will be screened but will not be routinely tested during this study.

**7.3 Study Assessments**

**7.3.1 Parameters**

Efficacy parameters to be assessed include; histological examination of scars following laser therapy, PROMS measured with BBSIP, subjective scar assessment (POSAS and mVSS) and objective scar assessment (scar thickness, density, pliability and colour)

**7.3.2 Blood Sampling**

Blood will be taken following local standard operating procedure (SOP) using venepuncture.

Blood samples will be analysed for pro and anti-inflammatory cytokines and scar biomarkers.

**7.3.3 Biopsies and Samples**

Tissue samples will be taken from the scar to be/has been treated with Laser therapy. The initial sample will provide a baseline histological profile of the scar tissue and subsequent samples will examine the changes in biomarkers associated with cellular senescence and scar formation including RNA molecules, senescent skin cells, TGF, decorin, VAPs, MMPs, PDGF, adiponectin, etc.

**7.3.3.1 Punch Biopsy Procedure**

The following procedure will be followed by the medical staff performing the punch biopsy:

- The intervention area will be injected with 1% Lignocaine (local anaesthetic) with 1:200,000 adrenaline before taking the scar biopsies. To supplement the topical anaesthetic amethocaine (Ametop) or EMLA cream 5% used before the laser therapy. The addition of local to topical anaesthesia will prevent the sharp pain that may not be alleviated by using the topical anaesthesia only.
- A 5mm punch biopsy will be taken from the hypertrophic scar to be treated with laser therapy (intervention area, control area and one biopsy from normal skin). Please see study schedule (Appendix A).
- Specimens will be divded and stored in Formalin and -80^▫^C freezer as per SOP.
- The specimen will be labelled “Specimen for clinical trial” and with patient unique trial number. The histological analysis will be performed at the UoB Laboratory.
- The wound will be redressed with a simple non-adherent dressing. The punch biopsy will not be closed using sutures as healing will occur naturally in a few days.
- The samples will be preserved in University of Birmingham Biobanks used for research
- The tissue biopsies will be handled and used appropriately as per Human Tissue Act (2004)

**7.3.4 Subjective Scar Assessments**

Patients will be requested to complete subjective scar assessments at each time point: Vancouver Scar Scale (VSS), Patient and Observer Scar Assessment Scale (POSAS, version 2.0) and Brisbane Burn Scar Impact Profile (BBSIP, version 1.0). These questionnaires are part of the standard of care in evaluating burns patients.

**7.3.4.1 Vancouver Scar Scale**

A version of the VSS that was adapted from the modified version used by Nedelec et al is used in this study. This scale uses a numerical assessment of four skin characteristics including: Height (range, 0-4), Pliability (range, 0-4), Vascularity (range, 0-3), and Pigmentation (range, 0-3). The assessors choose a numerical value for each of these characteristics based on a comparison with normal skin.

**7.3.4.2 Patient and Observer Scar Assessment Scale**

POSAS questionnaire seeks to measure scar quality. POSAS, version 2.0 is a subjective scar scale that consists of two parts: a Patient Scale and an Observer Scale. Both scales contain six items that are scored numerically on a ten-step scale and together they make up the ‘Total Score’ of the Patient and Observer Scale.

The POSAS Patient scale assesses the scar in terms of pain, itching, scar colour, stiffness, thickness and irregularity, and overall opinion.

**7.3.4.3 Brisbane Burn Scar Impact Profile (BBSIP)**

The Brisbane Burn Scar Impact Profile (BBSIP, version 1.0) is a questionnaire that was developed to assess the health-related quality of life in people with burn scars. It consists of seven parts which measure the overall impact of burn scars; itch, pain and other sensations (and their impact on the subject); impact of the burn scars on work and daily activities; impact of the burn scars on relationships and social interactions; subjects perception of the impact of the burn scars on their appearance; their emotional reactions towards their scars; and physical symptoms caused by the burn scars.

**7.3.4.4 EQ-5D**

The EQ-5D is a questionnaire used for measuring generic health status. The EQ-5D questionnaire consists of 5 questions relating to different domains of quality of life (mobility, self-care, usual activities, pain/discomfort, anxiety/depression) for each of which there are 3 levels of response (no problems, some problems or severe problems). The NICE guidelines state that the EQ-5D questionnaire is the preferred measure of health related quality of life in adults. The study participant will complete the EQ-5D questionnaire.

**7.3.5 Objective Scar Assessments**

**7.3.5.1 DSM III Colormeter**

The DSM III Colormeter (Cortex Technology) is a small handheld device which combines two methods of quantifying colour: narrow-band spectrophotometry (melanin, erythema) and tristimulus reflectance colorimetry in a single measurement. It has a skin measuring area of .7mm in diameter. It consists of a handheld probe which utilises two high intensity white LED lights and accommodates the colour sensor, filters, and optics. . Measurements are done by placing the probe over the selected area on the scar. The probe is to be held perpendicular to the scar using minimal pressure to avoid blanching of the scar.

**7.3.5.2 Dermascan C USB**

The Dermascan C USB (Cortex Technology) is a high-frequency (20MHz) ultrasound scanner that enables the imaging of soft tissue at high resolution with a computer, and comes with software that allows automated skin thickness measurement. A medium focus transducer will be used with a 12mm wide viewing field and penetration depth of 15mm.

Before measurement, a thin layer of conducting ultrasound gel will be applied to the transducer and the transducer is to be held perpendicular to the scar sites to record echographic images for each site.

All measurements are to be performed with an ultrasound frequency set at 1580m/s. Thickness and density (as a measure of total intensity in percentage) measurements are then generated using the dedicated software (Advance Control 6 Analysis SW package, Cortex).

The thickness measured is defined as the distance between the echogenic stratum corneum and the inner surface of the dermis (in millimetres).

**7.3.5.3 Cutometer**

The cutometer (MPA 580, Courage and Khazaka) is an electronic instrument that assesses skin elasticity. The probe of the device is placed over the area of measurement, and then generates a negative pressure which draws the skin into a hollow aperture in the centre of the probe and then uses a laser to estimate the amount of skin displacement.

The probe with a 6-mm diameter hollow aperture was chosen for this study as previous studies have determined it to be the most efficient size to measure the visco-elasticity properties of the dermis^16-18^. For this study, mode 1 was chosen. This delivers three cycles of negative air pressure (500 mbar) for 2 seconds, followed by 2 seconds of no pressure. Results are expressed as the means of the three measurement cycles.

**7.3.5.4 Vectra H1 3D Camera**

The Vectra H1 handheld imaging system delivers high resolution 3D images for clinical use. Three-dimensional (3D) measurement systems are used to overcome the limitation of 2D photograph, mostly used for clinical documentation. They can be utilised to measure surface area of wounds, but additionally be able to measure the volume of scars much more quickly and easily compared to traditional methods such as moulding.

The Vectra 3D camera has shown to be superior to other systems with a higher resolution and the utilision of an adjustable light-beam pointer to aid positioning and does not require single use disposable targets.

##

## 7.4 Clinical and Laboratory Assessments

**7.4.1 Laboratory Assessment**

Once the blood and tissue samples have been taken by the clinician or researcher at either site, the samples will be sent to the University of Birmingham (UoB) Research Laboratories based at the Queen Elizabeth Hospital Birmingham. The UoB laboratory will initially process the bloods and run a rapid testing for COVID-19 as a safety measure before they proceed in processing bloods for research. UoB lab is currently processing confirmed COVID-ve bloods. If the blood results turn out COVID+ve, the blood samples will be discarded in accordance with the Trust policy in disposing biological samples.

The delegated staff at Morriston Hospital, Swansea, Wales will initially process the blood samples and store them at -80^0^C and then send them frozen at University of Birmingham (UoB) Laboratories based at the Queen Elizabeth Hospital Birmingham (QEHB). The processing and storage of blood samples will be discussed in detail in the laboratory manual. The tissue biopsies will also be processed and stored in formalin and -80^▫^C freezer. The frozen samples will be stored and sent in batch through a designated courier to the UoB laboratory based at QEHB.

All samples will be sent with a linked anonymous form with no patient identifiable data. The link to the patients will be held on a screening log in the research office based at the QEHB. Tissue samples will be sent to the University of Birmingham laboratory, where some will be processed and analysed and some will be transferred to the HBRC biobank for long-term storage.

Serial collection of peripheral blood and tissue biopsies will be performed as summarised in Figure 1. Each sample will be extracted according to the respective SOP.

The list given below illustrates the key laboratory tests that will be performed on participant samples. However, the list is not exhaustive and may be modified during the ongoing analysis of data throughout the study.

**7.4.1.1 Analysis of Tissue**

Tissue samples will be taken from normal skin, scarred skin treated with laser (treatment area) and scarred skin not treated with laser (control area) for analysis.

Fresh collected biopsies will be split in half and kept in formalin and -80^▫^C freezer, respectively.

Depending on this initial processing, biopsies will be transferred and stored in: Formalin – QEHB/HBRC (tissue bank) – HBRC will further process the formalin fixed tissue, and paraffin embed them. Frozen samples stored in -80^0^C freezer and Cell dissociation solution – processed on the same day for immunophenotyping purposes.

We aim to identify novel markers associated with scarring and tissue regenerative capabilities such as markers of cellular senescence and DNA damage, for example p16 and ɣH2Ax and other biomarkers including micro RNAs, TGF-beta, decorin, VAP-1, MMPs, PDGF, adiponectin, etc.

Tissue samples will also undergo staining and immunostaining as part of the histological analysis. H&E stain, Movat’s pentachrome stain, Herovici’s staining, amongst others, will be used to process epidermal and dermal height, inflammation, collagen orientation and thickness.

Immunostaining of tissue will be used to assess markers of inflammation and  regeneration, for example identification of types of collagen, smooth muscle actin, markers of angiogenesis or microvasculature (CD31), neutrophils (CD15), macrophages (CD68) and keratinocyte staining (CK 10, CK14) are to name a few.

The initial sample will provide a baseline histological profile of the scar tissue and subsequent samples will examine the collagen arrangement and fibrosis with and without laser therapy.

**7.4.1.2 Analysis of Blood**

Soluble markers will be sourced from blood which is processed to serum (6mls) and plasma (4.5 mls). For Morriston Hospital, an additional blood sample of 4.0 ml using EDTA tube will be collected for full blood count.  We aim to identify expressions and markers that influence scar formation, wound healing and variables of scar behaviour in response to CO_2_ laser therapy. This will include pro and anti-inflammatory cytokines, scar biomarkers and markers of cellular senescence, for example mmp.

Serum will be prepared by the centrifugation of blood collected into tubes containing z-serum clot activator. To measure plasma cfDNA, trisodium citrate anticoagulated blood will be 20 minute spin at 2,000 x g at 4 degrees and then collect the supernatant from the first spin and then spin at t 13,000 x g for 2 minutes at 4 degrees.

**7.4.2 Storage and disposal of samples**

This study will include the use of newly obtained blood (serum and plasma) and tissue samples provided by the participant. The samples will be collected by a trained research nurse or clinician. Once collected, the samples will be processed at the University of Birmingham by a member of the research team.

Aliquots of serum and plasma will be stored at -80°C in linked anonymised form in which the donor will not be identifiable to researchers. The samples will be stored in the University of Birmingham Laboratories based at the Queen Elizabeth Hospital.

Some of the skin biopsy samples will be stored in University of Birmingham biobanks. University Hospital Birmingham Samples will be used for various measurements as part of the study. Once the study has concluded, samples will be stored for future research in the biobanks.

All samples will be anonymised prior to transfer to the UoB Laboratory where they will be processed, stored and destroyed in accordance with the Human Tissue Act (2004) as described above. All samples will be kept until 10 years after analysis is completed.

**7.5 Schedule of Assessments and Data Collection**

**7.5.1 Baseline Data Collection (Recruitment/pre-assessment)**

Before any study related data or specimens are taken, the researcher will ensure that informed consent has been obtained and confirm that the trial subject meets the inclusion and non of the exclusion criteria. The study personnel will then collect and record the following information in the paper CRF booklet and eCRF (electronic case report form):

- Baseline patient information (age, sex, ethnicity, comorbidities, pre-injury medications)
- Burn/ trauma mechanism e.g. flame, scald etc.
- Anatomical location of scar to be treated with Laser therapy (wound map)
- Medical co-morbidities including Psychiatric or Behavioural Problems
- Subjective scar questionnaires - VSS, POSAS, BBSIP, QoL questionnaire (EQ-5D)
- Objective scar assessments – 3D camera, DSMII Colorimeter®, Dermascan® & Cutometer®.
- Clinical photograph of area of interest (treatment and control)
- Blood sample
- 2 Punch Biopsies (5mm) of scar tissue from identified sites that will be randomised for control and treatment area
- Punch Biopsy (5mm) of comparable normal skin.

**7.5.2 First laser intervention (Day 1)**

- Adverse events

**7.5.3 Post 1^st^ laser intervention (Day 22 +/- 3 days)**

- Clinical assessment and post laser care
- Clinical photographs
- Adverse events
- Punch Biopsy (5mm) only intervention area.
- Blood sample

**7.5.4 Second laser intervention (3 months +/- 30 days)**

The following clinical examinations and data will then be collected and recorded in the eCRF:

- Adverse events
- Blood sample
- Clinical photograph
- Subjective scar questionnaires – VSS, POSAS, BBSIP, EQ-5D
- Objective scar assessments – 3D camera, DSMII Colorimeter®, Dermascan® & Cutometer®

**7.5.5 Third laser intervention (6 months +/- 30 days)**

The following clinical examinations and data will then be collected and recorded in the eCRF:

- Adverse events
- Punch Biopsy (5mm) of intervention area (Pre 3^rd^ intervention) only. (No control or normal skin biopsies.)
- Blood sample
- Clinical photograph
- Subjective scar questionnaires – VSS, POSAS, BBSIP, EQ-5D
- Objective scar assessments – 3D camera, DSMII Colorimeter®, Dermascan® & Cutometer®

**7.5.6 Follow-up Visit (6 months post 3^rd^ ^t^ Laser Treatment +/- 30 days)**

The following clinical examinations and data will then be collected and recorded in the eCRF:

- Adverse events
- Punch biopsy 5mm of **both** the intervention and control areas.
- Blood sample
- Clinical photograph
- Subjective scar questionnaires - VSS, POSAS, BBSIP, EQ-5D
- Objective scar assessments – 3D camera, DSMII Colorimeter®, Dermascan® & Cutometer®

# DATA MANAGEMENT & STATISTICS

## Determination of Sample Size

**8.1.1 Laser Treatment and Standard of Care**

Following recommendations for pilot studies, 30 patients or more are typically required to gain estimates of the parameters needed for sample size estimation. No formal sample size calculation has been performed as a result. We have allowed for a 20% drop-out and possible loss to follow-up. We therefore aim to recruit 60 participants in total. This will also allow the recruitment and retention rates to be estimated with 95% confidence interval maximum widths of 20% and 25% respectively.

## Statistical Analysis

The primary comparison groups will be the scar sections randomised to (control group) versus those randomised to treatment with laser therapy (experimental group). Outcome data will be collected at pre-laser, 3 weeks post the first and third treatments and 12 month

s post third treatment.

All analysis will be based on the intention to treat principle, i.e. all scars will be analysed in the treatment group to which they were randomised irrespective of compliance with the allocated treatment or other protocol deviation. The data analysis for this pilot trial will be descriptive and mainly focus on confidence interval estimation, with no formal hypothesis testing performed.

Dichotomous feasibility measures, like the recruitment and retention rates, including completeness of data will be reported as numbers and percentages. These values will be summarised across participants or treatment groups as appropriate.

Given this study is a pilot, the data will help inform the selection of the most appropriate primary outcome measure for a larger RCT and provide data to estimate the sample size required for the main RCT.

Analysis methods will be chosen according to the data type; 1. Continuous endpoints (e.g. VSS total score): These data will be summarised using means and standard deviations, with differences in means with 95% confidence intervals reported. Longitudinal plots of the data over time will also be constructed for visual presentation of the data. 2. Categorical (dichotomous) endpoints (e.g. rates of improvement in scar domains): The number and percentages of participants/scars experiencing the event will be summarised across and between groups.

As this is a randomised study, there are no priori subgroup analyses specified.

Every attempt will be made to collect full follow-up data on all study participants with the anticipation that missing data will be minimal. The assessment of missing data is an outcome measure of this study.

If a suitable primary outcome is identified during the pilot trial, the level of missing data will form one component of the assessment of feasibility for a future trial. As this is a pilot trial, no formal sensitivity analysis will be conducted.

The primary analysis for the trial will occur once all participants have completed the 12 month assessment and corresponding outcome data has been entered onto the trial database, validated as being ready for analysis, and the database locked. This analysis will include data items up to and including the 12 month assessment.

For the secondary outcome data about the biomarkers of the scar response to laser therapy the various cellular and molecular variables will be examined for relationships to scarring using logistic regression. Further longitudinal analysis to identify potential drivers of a positive response will be done using linear mixed-effects modelling.

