# STUDY OBJECTIVES

## Objectives

- - 1. **Primary Objectives**

To assess the kinetics of the response to fractionated CO_2_ laser therapy in hypertrophic scars, in particular to test the hypothesis that a positive effect on the scar (assessed through objective and subjective measures) is associated with reduced number of myofibroblasts and the increased presence of senescent skin cells.

- - 1. **Secondary Objectives**

To determine associations between the various cellular and molecular biomarkers and reduction in scarring post laser therapy.

To evaluate the extent to which the use of Brisbane Burn Scar Impact Profile (BBSIP) is a sound psychometric measure of improvements in scarring and the impact on participant’s quality of life as a result of laser treatment.

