## 2.2 Study Endpoints

**2.2.1 Primary endpoints**

The primary endpoint is to assess the effect of the ablative carbon dioxide laser therapy via histological assessment of the hypertrophic scarring and in particular using novel methodology to detect the number of senescent cells and the subpopulation of fibroblast 6 months after the third laser treatment.

Scars will be assessed histologically (5mm punch biopsy) to assess dermal and epidermal thickness, collagen structure and orientation, elastin density and structure. Immunostaining will examine possible scar biomarker, proportion of senescent cells and the proportion and sub-population of fibroblasts following treatment.

To identify novel markers associated with scarring and tissue regenerative capabilities such as markers of cellular senescence and DNA damage, for example p16 and ɣH2Ax and other biomarkers including: micro RNAs, TGF-beta, decorin, VAP-1, MMPs, PDGF, adiponectin, etc.

To identify expressions and markers both in blood and tissue samples that influence scar formation, wound healing and variables of scar behaviour in response to CO_2_ laser therapy. This will include; pro and anti-inflammatory cytokines, scar biomarkers and markers of cellular senescence, for example mmp.

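### The primary objective is to test a cellular hypothesis, but section 8.2 rules out testing, labels the biomarkers secondary and ties no analysis to that association

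*Protocol*

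**What the plan says.** Protocol section 2.1.1 (Primary Objectives) sets out "to test the hypothesis that a positive effect on the scar (assessed through objective and subjective measures) is associated with reduced number of myofibroblasts"; more senescent skin cells form the other half of the hypothesis. Section 2.2.1 (Primary endpoints) is a histological assessment meant to "detect the number of senescent cells and the subpopulation of fibroblast 6 months after the third laser treatment". The same section adds a wide marker search: "To identify novel markers associated with scarring and tissue regenerative capabilities such as markers of cellular senescence and DNA damage", followed by further tissue and blood markers. Section 2.1.2 separately lists, as a secondary objective, the associations between biomarkers and reduction in scarring.

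Section 8.2 (Statistical Analysis) makes four statements that bear on this:

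- The analysis is descriptive and centred on confidence intervals, "with no formal hypothesis testing performed".
- The primary comparison is laser-randomised against control-randomised scars. Continuous endpoints are reported as mean differences with 95% intervals.
- The biomarkers are introduced as secondary: "For the secondary outcome data about the biomarkers of the scar response to laser therapy the various cellular and molecular variables will be examined". The method named for this is a logistic regression, with scarring as the outcome.
- A further longitudinal analysis, by linear mixed-effects modelling, will look for what drives a good response.

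Section 8.2 names neither myofibroblasts nor senescent cells.

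**The concern.** Sections 2 and 8.2 disagree on two things that a protocol has to settle: whether the primary hypothesis is tested or only estimated, and whether the cellular markers are primary or secondary. With both versions in force, a clear association could be reported as a confirmed primary hypothesis and a weak one as exploratory pilot data, and either report would be consistent with the protocol.

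The stated association method adds to this. Logistic regression needs a binary outcome. Section 8.2 gives no scale, cut-off or time point for scarring, so the outcome itself could be settled after the data are seen. Any cut-off also discards information from scales that are already collected in full.

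**Working it through.** No stated figure decides this point, so the main check sets the sections side by side.

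| Question | Section 2 | Section 8.2 |
| --- | --- | --- |
| Is the hypothesis tested? | Yes (2.1.1) | No formal testing |
| Status of cellular markers | Primary endpoints (2.2.1); marker associations also a secondary objective (2.1.2) | Secondary |
| Laser effect on cell measures | Primary endpoint (2.2.1) | Covered generically by the mean difference with 95% interval |
| Association of scar change with myofibroblasts and senescent cells | Primary objective (2.1.1) | No analysis names it |

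The last row is the gap. A laser-minus-control difference in cell measures shows whether laser changes the cells. It does not show whether patients whose scars improve more are those whose cells change more. Two methods in 8.2 could address that:

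- If the logistic regression serves the secondary objective in 2.1.2, which its wording resembles, the primary association has no named analysis.
- If it serves the primary objective, the secondary label is wrong.
- The mixed model could carry the association, but it is tied to no cell type and no scar measure.

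**Scale of the outcome.** By section 7.3.4.1 the Vancouver scale has ranges 0–4, 0–4, 0–3 and 0–3, so its total runs from 0 to 4 + 4 + 3 + 3 = 14. Each part of POSAS has six items on a ten-step scale (7.3.4.2). Ultrasound thickness is in millimetres (7.3.5.2), and the cutometer result is a mean of three cycles (7.3.5.3). None of these is binary.

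**Illustration of what a split could cost.** Inputs from the protocol: 60 patients and 20% drop-out (8.1.1), so 60 × 0.80 = 48. Assumptions that are not in the protocol: a true correlation of 0.4, one row per patient, and a split at the median.

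- Information kept by a median split: 2/π = 0.637, and 48 × 0.637 = 30.6, or about 31 patients' worth.
- Continuous outcome, Fisher z: atanh(0.4) × √(48 − 3) = 0.424 × 6.708 = 2.84. The chance that the 95% interval excludes zero is Φ(2.84 − 1.96) = 0.81.
- Split outcome: the correlation shrinks to 0.4 × √(2/π) = 0.319. Then atanh(0.319) × 6.708 = 2.22 and Φ(2.22 − 1.96) = 0.60.
- Simulation (20,000 runs) gave 0.82 and 0.61, in agreement.

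**What estimation would deliver with 48 patients** (tanh[atanh(r) ± 1.96/√45], r assumed):

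| r | 95% interval |
| --- | --- |
| 0 | −0.28 to 0.28 |
| 0.3 | 0.02 to 0.54 |
| 0.5 | 0.25 to 0.69 |

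This is usable for a pilot, provided it is presented as estimation.

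**Feasibility of a within-patient analysis.** Both scars are biopsied at baseline (7.5.1) and at the final visit (7.5.6). At Day 22 (7.5.3) and Month 6 (7.5.5) only the laser site is biopsied. A laser-minus-control contrast in tissue change is therefore possible at the final visit only. The intermediate biopsies need the longitudinal model.

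**The case against.** The strongest reply is that this is a pilot. Ruling out formal tests and reporting intervals is normal there, and model details may sit in an analysis plan that is not shown. The secondary label also has a home, since 2.1.2 lists biomarker associations as a secondary objective. The mean difference in 8.2 covers the laser effect on histology. All of this stands. It does not remove the conflict, because 2.1.1 still promises a test that 8.2 excludes, and 2.2.1 still lists as primary the markers that 8.2 calls secondary. An analysis plan cannot settle which section of the protocol governs.

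Four stronger readings are tempting, and the protocol does not support them:

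- *Logistic regression is the only method offered.* The next sentence of 8.2 adds linear mixed-effects modelling, which takes continuous outcomes and can carry the pairing of scars within a patient.
- *Paired scars are treated as independent, so standard errors are wrong.* Section 8.2 does not state the unit of analysis or how clustering is handled, and a protocol may leave that to an analysis plan.
- *This trial's own primary outcome is still to be chosen.* The selection described in 8.2 is for a later, larger trial.
- *The many markers imply a known false-positive rate.* Such a figure needs 5% tests and a count of independent markers. The protocol excludes formal testing and leaves the marker list open.

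**Conclusion.** The point holds as a contradiction about what is primary and whether it is tested, together with the lack of any analysis tied to the primary association and a logistic model whose binary outcome is undefined. It should be fixed. It does not invalidate the design, because the data needed for a sound analysis are already scheduled.

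The contradiction rests on the protocol text alone and needs no assumption. The fall from about 82% to 61% is illustrative: it depends on an assumed correlation of 0.4, 48 evaluable patients and a median split, none of which the protocol specifies for this analysis. A different cut-off, or a responder definition based on improvement, would give another figure.

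**What to change.** 1. In 2.1.1, replace testing the hypothesis by estimating the association, in line with 8.2.
2. Align the labels in 2.2.1 and 8.2. Name the senescent-cell proportion and the myofibroblast measure at 6 months after the third laser as the primary variables. Report each as the within-patient laser-minus-control difference in change from baseline, with a 95% interval. Label the other tissue and blood markers exploratory, consistent with the secondary objective in 2.1.2.
3. In 8.2, replace the logistic regression by a linear model of continuous scar change. Use one row per patient: the laser-minus-control difference in scar change at the final visit, regressed on the matching difference in the marker, with 95% intervals. State which scar measure is used.
4. Keep the planned linear mixed-effects model, with a patient random effect, for the serial laser-site biopsies.

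The cost is wording and a little analysis work, with no new visits or samples. The downside is that odds ratios for responders become supportive only.
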